## Methods

### Study design

This study is a superiority randomized controlled trial with multiple arms: two experimental groups and one care-as-usual-only as the control group. Based on equivalence, the two intervention groups receive care-as-usual plus a mentoring intervention called Mentor Support. The difference between these two groups is determined by the VI of the mentors and not by the way Mentor Support is performed. One group receives Mentor Support from a mentor with a visual impairment and one group from a sighted mentor. The effectiveness of this randomized controlled trial will be tested with pre-test, post-test, and follow-up. This study protocol has been approved by the Ethics Committee of the VU University (VCW.1310.010; Netherlands Trial Register NTR4768).

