### Sample size

The total sample size is based on the expected differences in outcome measures between participants assigned to the experimental arm receiving Mentor Support and the care-as-usual-only arm. For testing the significance of the between-subject factor (primary hypothesis) a sample of 120 participants (40 in each condition) is necessary to achieve an adequate power of .85 within a medium effect size (d = .5) between the conditions over time with a significance level of .05. Due to dropout or unexpected organizational aspects the number of participants could drop to as low as 108 to achieve a high power of .80. To answer the research question concerning the influence of potential mediators or predictors on the effectiveness of Mentor Support, several repeated measures within-between interaction analyses will be performed. Based on a significant level of .05 and a power of .85 (*f* = .25), a total sample size of 110 is needed.

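### Sample size: the totals 120 and 108 reproduce exactly with f = .25, the two-group conversion of d = .5; with three equal arms d = .5 gives f of at most .236, so the stated power may be too high

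*Protocol article*

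**What the plan says.** The design has "two experimental groups and one care-as-usual-only as the control group" (Study design), allocated 40:40:40. The Sample size section gives the primary calculation as: "For testing the significance of the between-subject factor (primary hypothesis) a sample of 120 participants (40 in each condition) is necessary". That total is said to be "necessary to achieve an adequate power of .85 within a medium effect size (d = .5) between the conditions over time", at alpha .05. On dropout it adds that "the number of participants could drop to as low as 108 to achieve a high power of .80".

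No f, number of measurements or correlation is given for that calculation. The only f in the section belongs to the separate calculation for mediators and predictors: "Based on a significant level of .05 and a power of .85 (*f* = .25), a total sample size of 110 is needed".

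Three other places bear on which test is meant:
- The main hypothesis, and the opening sentence of the Sample size section, set Mentor Support against care-as-usual only.
- The Data analyses section compares each mentor arm separately with care-as-usual.
- The abstract gives three measurements: pre-test, 12 months and 18 months.

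**The concern.** Cohen's f for a between-subject factor depends on how the group means are spread. Halving d is right for two equal groups only. In a three-arm test the same d always gives a smaller f, so entering d/2 overstates power. The article names d = .5, yet its totals are those that f = .25 produces in a three-arm test.

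The dropout allowance is what is at stake. The article allows the sample to fall from 120 to 108 with power still at .80, and its Discussion names selective attrition over 18 months as a limitation. If the conversion was wrong, that margin is already used up at 120, and a null result would seem to rule out a medium effect with more assurance than the design gives.

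**Working it through.** **Inputs from the article:** d = .5; alpha .05; three equal arms (k = 3); N = 120 or 108; three measurements (m = 3, abstract). **Assumed:** correlation between measurements rho, which the article does not state. I use .5 first because it reproduces the totals, then vary it.

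**Formula.** For the between-subject factor of a repeated-measures ANOVA, power comes from the noncentral F distribution with k − 1 and N − k degrees of freedom and

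lambda = f² × N × m / (1 + (m − 1) × rho).

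**Step 1: reproduce the stated figures.** Take f = .25, m = 3, rho = .5, so that 1 + 2 × .5 = 2.
- N = 120: lambda = .0625 × 120 × 3 / 2 = 11.25; power .851.
- N = 108: lambda = .0625 × 108 × 3 / 2 = 10.125; power .809.

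The smallest balanced totals are exactly 120 for .85 and 108 for .80. One set of inputs gives both printed totals.

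**Step 2: convert d = .5 for three equal arms.** f is the standard deviation of the three group means in units of the within-group SD.
- Both mentor arms .5 above control, means (.5, .5, 0): f = .5 × √2 / 3 = .2357. This is the largest f possible when the widest difference is .5. It also matches the secondary hypothesis that the two mentor arms improve equally.
- Evenly spaced means (.5, .25, 0): f = .5 × √(1/6) = .2041.
- d needed for f = .25: .25 × 3 / √2 = .530.

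This step depends on neither rho nor the number of waves.

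**Step 3: the same test with the three-arm f** (m = 3, rho = .5).
- f = .2357, N = 120: lambda = .05556 × 120 × 3 / 2 = 10.0; power .805.
- f = .2357, N = 108: lambda = 9.0; power .758.
- Totals needed at f = .2357: 120 for .80 and 135 for .85.
- f = .2041: power .676 at 120 and .625 at 108.

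**Step 4: other readings, all at d = .5.**

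| Test | Waves | rho | Power at 120 | Power at 108 |
|---|---|---|---|---|
| Three-arm F, f = .2357 | 3 | .3 | .888 | .850 |
| Three-arm F, f = .2357 | 3 | .39 | .851 | .808 |
| Three-arm F, f = .2357 | 3 | .5 | .805 | .758 |
| Three-arm F, f = .2357 | 3 | .7 | .725 | .674 |
| Mentor arms pooled v control (80 v 40; 72 v 36) | 3 | .5 | .880 | .844 |
| Mentor arms pooled v control | 3 | .6 | .849 | .809 |
| Mentor arms pooled v control | 2 | .5 | .841 | .800 |
| Each mentor arm v control (40 v 40; 36 v 36) | 3 | .5 | .772 | .727 |

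At rho = .39 the three-arm F test with the correct f also has 120 and 108 as its exact smallest totals. The pooled contrast comes close to the stated powers but falls just short of .85 at 120, both with three waves and rho = .6 and with two waves and rho = .5. With three waves and rho = .5 it would need only 111 and 99.

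**The case against.** The strongest reply is that the error is not on the page. The article prints no f, number of waves or correlation for the primary calculation, and its one printed f belongs to another analysis. That analysis is weak support: its total of 110 does not come out as a three-arm, three-wave interaction (39 would suffice at rho = .5). The match in step 1 is also not unique. With the correct f and rho = .39 the same test gives the same two totals, and a pooled contrast at rho = .6 gives .849 and .809. The main hypothesis and the opening of the Sample size section describe a comparison of Mentor Support with care-as-usual, which fits a pooled contrast at least as well as a three-arm F test. At rho = .5 that contrast exceeds both stated powers.

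All of this stands. A reader might infer that the article is shown to have miscalculated, or that .85 and .80 cannot be reached for d = .5. The text supports neither reading, because one unstated correlation or an unstated choice of contrast separates an error from a correct figure.

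The reply does not remove the point. The inputs that give both totals exactly are f = d/2 with rho = .5, or the correct f with a correlation near .39 that the article nowhere mentions. The pooled readings miss one total slightly. The separate comparisons planned under Data analyses have about .77 and .73 at rho = .5, though for a different reason: each uses only two of the three arms.

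**Conclusion.** The concern holds in a conditional form. What is certain is the conversion: with three equal arms and a largest difference of d = .5, f cannot exceed .236, and f = .25 corresponds to d = .53. What is likely but inferred is that d = .5 was entered as f = .25.

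If the calculation was a three-arm, three-wave F test with rho = .5, power for d = .5 is about .80 rather than .85 at 120, and about .76 rather than .80 at 108. The shortfall is 4 to 5 percentage points, and the stated allowance for losing 12 participants is not available for d = .5. These figures assume both mentor arms lie .5 above control; any other pattern with the same largest difference gives the same power or less. If a pooled contrast or a correlation near .39 was used, the stated powers are met, or missed by at most about one percentage point, and only the inputs need to be printed.

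**What to change.** In the Sample size section, name the test behind 120 and 108, and print its f, number of measurements and assumed correlation.

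If f = .25 was entered, do one of two things:
- state that the trial is sized for d = .53; or
- keep d = .5, report power of about .80 at 120 and .76 at 108 (with rho = .5), and remove the statement that 108 keeps .80.

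If another test or correlation was used, printing it settles the matter and the powers need no change beyond rounding. The cost is one or two sentences and, at worst, a slightly less favourable stated power. No extra recruitment is needed.

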#### Predictor variables

Predictors that might distinguish adolescents who benefit from the interventions include demographic factors and personality.

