One limitation inherent in this study may be the risk of selective attrition during the relatively long period of 18 months for which the participants are connected with the study. During the Mentor Support intervention mentees could drop out of the study for several reasons, such as moving to another part of the Netherlands, parental concerns, or health reasons. Dropout from the care-as-usual-only group may occur directly after the primary researcher has informed them about the results of the randomization and after 12 months with T2. All participants receive and sign an informed consent whereby they are informed in advance about the possibility of ending up in the care-as-usual-only group. This is also mentioned in the first letter or brochure that they receive. This may prevent dropout from the care-as-usual-only group. Another limitation of this study could be the relatively small sample size, due to the small population size. This could lead to problems with making firm conclusions about predictors and mediating study findings. Finally, a limitation could be to find enough mentors in the same region of the country where the participant lives. In this case more mentors are probably needed than the number 40 that we have described above.

In conclusion, this study will gain knowledge about the effectiveness of a mentoring intervention (Mentor Support) for adolescents with visual impairments to improve their social participation. Three conditions are included to test the importance of disability-specific experience. In addition, this study will also give more insight into the pathways to successful social participation, several predictors, and the mediating effects of psychosocial functioning and self-determination.

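### The .85 power at 110 participants is that of an arm-by-time interaction: it is unsupported for mediation, and for predictors of benefit it holds only if subgroups differ far more than the assumed main effect

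*Protocol article*

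**What the plan says.** The Sample size section first sizes the trial for the primary comparison: 120 participants for power .85 at d = .5, with 108 tolerated at power .80. It then turns to "the influence of potential mediators or predictors on the effectiveness of Mentor Support, several repeated measures within-between interaction analyses will be performed". For these analyses it continues: "Based on a significant level of .05 and a power of .85", with f = .25, "a total sample size of 110 is needed". It does not say which model term f = .25 describes.

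Other sections show what the question is. Predictor variables introduces "Predictors that might distinguish adolescents who benefit from the interventions", namely demographic factors and personality. The third secondary hypothesis expects more improvement in social participation among mentored adolescents who are self-determined or function well psychosocially. Both are questions of effect modification. The Trial objective and Discussion sections also ask whether psychosocial functioning and self-determination mediate the effect. On the small sample, the Discussion concedes: "This could lead to problems with making firm conclusions about predictors and mediating study findings".

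**The concern.** A within-between interaction of arm and time asks whether the arms follow different courses on one variable. Asking who benefits needs a further interaction with the predictor. Asking through what the benefit comes needs an indirect effect: arm to mediator, then mediator to outcome given arm. The article attaches one power figure to all of this, and neither a predictor nor an indirect effect enters the calculation as described.

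Predictors and pathways are stated secondary aims. A null result (personality does not matter, self-determination does not mediate) could be defended by pointing to a stated power of .85 that the analysis may never have had.

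**Working it through.** **Inputs from the article.** Three equal arms (k = 3); three measurements at pre-test, 12 and 18 months (m = 3); alpha .05; f = .25; power .85; N = 110; main effect d = .5.

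**Assumed, because the article gives no value.** Correlation between measurements rho = .5 (.7 as a check); a predictor splitting the sample 50/50; path a (effect on the mediator, pooled mentoring v control) d = .5, or .5/sqrt(1 - .25) = .577 after baseline adjustment at rho = .5; path b as a partial correlation of .2, .3 or .39.

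**1. Reproducing 110.** Noncentral F with lambda = f^2 x N x (m - 1), df1 = (k - 1)(m - 1) = 4 and df2 = (N - k)(m - 1).
- N = 110: lambda = .0625 x 110 x 2 = 13.75, df2 = 214, power .851.
- N = 109: power .847.

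The smallest N for .85 is therefore 110. The other common convention, lambda = f^2 x N x m/(1 - rho), needs only 39 at rho = .5 and does not reproduce it.

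**2. The same f placed on arm x predictor x time.** With a binary predictor, df1 = 4 and df2 = 2(N - 6) = 208. Lambda is again 13.75 and power again .851, so the arithmetic cannot tell which term was meant.

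**3. What that f implies for predictors.** If the two halves differ in effect by as much as the main effect, f for the three-way term is .25 x sqrt(.5 x .5) = .125.
- Lambda at 110 = .015625 x 110 x 2 = 3.44; power .27.
- N for .85 = 432.
- To reach f = .25 the subgroup difference must be twice the main effect.

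**4. The same in SD units.** Let the benefit appear at 12 months and persist at 18, and differ by delta between halves in both mentored arms. Then lambda = (N/27) x delta^2/(1 - rho).
- rho = .5, delta = .5: lambda = 4.074 x .25/.5 = 2.04; power .17.
- delta = .75: power .36. delta = 1.0: power .60.
- delta = 1.3: lambda = 13.77; power .85.
- rho = .7, delta = .5: power .27.

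**5. A single pooled contrast (mentored v control).** The standard error of the main contrast is sqrt(3/110 + 3/220) = .2023 SD. For a difference between halves it doubles to .4045 SD. With rho = .5 and delta = .5:

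| Analysis | SE | Power | Detectable at .85 |
|---|---|---|---|
| Change score | .405 | .23 | 1.21 SD |
| 12 months, adjusted for baseline (x sqrt .75) | .350 | .30 | 1.05 SD |
| Mean of 12 and 18 months, adjusted (x sqrt .5) | .286 | .42 | 0.86 SD |

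**6. Mediation by joint significance.** Power is approximately power(a) x power(b), where power(a) = Phi(d/.2023 - 1.96) and power(b) = Phi(atanh(r) x sqrt(106) - 1.96).
- Path a: d = .5 gives .70; d = .577 gives .81.
- Path b: .2 gives .55; .3 gives .89; .39 gives .99.
- Joint, d = .5: .38, .62, .69. Joint, d = .577: .45, .72, .80.

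Joint power cannot exceed that of path a. With d between .5 and .577 it therefore stays below .85 whatever path b is.

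**The case against.** The best defence is that 110 is not an arithmetic error. It reproduces exactly, and step 2 shows that it also reproduces if f = .25 describes the arm x predictor x time term. A reader might infer that the trial flatly lacks .85 power to show who benefits. The article does not support that, because it gives no expected subgroup difference against which .85 could be called false. This stands, and it limits the point on predictors to an unstated and very demanding condition.

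It can also be said that the low power figures rest on assumptions made for this check. That is fair. Under the other lambda convention, f = .125 at 110 gives .40, .55, .72 and .93 for rho = 0, .3, .5 and .7. But that convention does not yield the article's 110, and in the pattern of step 4 its f = .125 corresponds to a difference of about 1.1 SD, not .5.

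A reader might also set 110 against the statement that "the number of participants could drop to as low as 108" and see a contradiction. There is none of substance: 108 is tied to .80 power for the primary test, and the arm-by-time power at 108 is .843 against .851.

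Last, the Discussion already warns about firm conclusions, these aims are secondary, and the planned sample does not rest on 110. That lowers the stakes. Yet the warning conflicts with the .85 in the Sample size section and does not correct it. The details of a mediation model can be left to an analysis plan. A power figure already attached to the wrong question is a different matter.

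**Conclusion.** The point holds in a limited form. The pair 110 and .85 is right for arm-by-time change in any one variable, including each mediator as an outcome.

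- **Mediation:** the figure is unsupported, because the test it sizes is not a test of an indirect effect. Joint-significance power at 110 is about .38 to .80 under the assumed paths.
- **Predictors of benefit:** the figure is conditional on f = .25 belonging to the three-way term, a subgroup difference about twice the main effect or more (1.3 SD in step 4 at rho = .5). For a difference equal to the main effect, power is about .2 to .3 (.17 to .30 across most of the analyses shown), and .42 with the most efficient pooled contrast.

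The exact values depend on the assumed correlation, split and paths. The mismatch between test and question does not.

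**What to change.** In the Sample size section:
- State that 110 and .85 refer to the arm-by-time change in each mediator or outcome.
- Withdraw the .85 for mediation and for predictors of benefit. Alternatively, replace it with the power of the indirect effect and the detectable difference for the arm x predictor x time term, each under the sponsor's own stated assumptions. The values used in this check need not be adopted.
- Label these analyses exploratory and report them as estimates with confidence intervals, in line with the limitation given in the Discussion.

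The cost is a few sentences and a less favourable stated power. No extra participants are needed and the design does not change.

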### Selective attrition

All participants will be expected to participate in pre-test, post-test, and follow-up during this study. All those who drop out of the study during Mentor Support or from the care-as-usual-only group will be measured for post-test and will be followed up if possible. Dropout reasons will be documented and analyzed in order to use this information for improvement of the execution of the intervention. To account for selective attrition, intention-to-treat analyses will be performed.

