### Procedure

#### Mentees

Participants will be recruited through two national service organizations (Bartiméus and Royal Dutch Visio) for people with VI. These organizations have multiple rehabilitation centers, have special education schools all over the Netherlands, and also offer itinerant teacher support to adolescents with VI in regular education. These organizations will send a recruitment brochure and cover letter to inform all clients/students who meet the inclusion criteria and their parents. Clients/students who do not participate will remain anonymous to the researcher. Participants are also to be recruited through online banners, brochures on social media, Internet/magazine/website advertisements, and brochures distributed by several associations for people with VI.

If participants decide to participate, they sign up for this study, with their name and email address, via the website. After signing up, the participants are asked questions about demographic factors, their visual impairment, and possible additional impairments. If participants meet the inclusion and exclusion criteria for this study, they and their parents (if the participant is under 18) receive an official information letter and informed consent form. After signing and sending back the informed consent, they are then eligible to participate in this study. Because signing and sending back the signed informed consent could be challenging for people with VI, participants are allowed to sign the consent form by placing a cross (X) in a box and sending it back by email. Printing and signing by hand is therefore not needed. This procedure has been established with the approval of the Ethics Committee of the VU University.

Once the informed consent is sent back to the researchers, participants receive a baseline measurement (T1). Data will be collected in the Netherlands in their own home environment through computer-assisted telephone interviews. These interviews are conducted by several trained researcher assistants using online survey software called Qualtrics. An interview lasts about one hour and 30 minutes and contains several questionnaires. After this baseline measurement, every participant is randomly allocated to one of the experimental groups or the care-as-usual-only group. The results from the randomization will be sent to the participants in the experimental group (mentees) by email, and the care-as-usual-only group will be informed by telephone.

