### Randomization

Upon signing the informed consent, before randomization, participants agree to be allocated to one of the three groups. An independent researcher will randomly assign participants at an individual level to one of the three arms of this randomized controlled study. The allocation will take place with a computerized random number generator after the baseline measurement and before the start of the intervention. Randomization stratification on the important factor of geographic proximity will be used to make sure there is equal allocation to regions. Blocking randomization in each region with a block size of 15 participants will be used to strive for regional groups with the same size. The independent researcher will keep the results of the randomization until the study is completed and all eligible participants are allocated. During the study the primary researcher and participants are not blinded. Only the researchers measuring the post-test and follow-up will be unaware of who is allocated to which arm.

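### Intention-to-treat is named as the remedy for selective attrition, but it does not correct for outcomes that are never obtained

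*Protocol article*

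**What the plan says.** The Selective attrition section names one analytic remedy: "To account for selective attrition, intention-to-treat analyses will be performed". The same section says that people who drop out of any arm "will be measured for post-test and will be followed up if possible". On the reasons for leaving it says: "Dropout reasons will be documented and analyzed in order to use this information for improvement of the execution of the intervention".

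The Discussion returns to the subject: "One limitation inherent in this study may be the risk of selective attrition during the relatively long period of 18 months". It gives mentees reasons such as relocation, parents' worries or illness. For controls it describes something else: "Dropout from the care-as-usual-only group may occur directly after the primary researcher has informed them about the results of the randomization", and again at the 12-month assessment. It then points to the advance information given at consent and in the first letter or brochure, and adds: "This may prevent dropout from the care-as-usual-only group".

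Three other places bear on this:

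- **Procedure, Mentees:** "After this baseline measurement, every participant is randomly allocated to one of the experimental groups or the care-as-usual-only group".
- **Randomization:** "During the study the primary researcher and participants are not blinded".
- **Data analyses:** the model may be either repeated-measures ANOVA or a multilevel analysis. The Abstract lists ITT and completer analyses as two separate analyses.

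**The concern.** ITT is a rule about allocation: each person is analysed in the arm to which they were randomised. It says nothing about an outcome that nobody recorded. Whether a leaver without outcome data enters the analysis at all, and on what assumption, is decided by the model and the handling of missing data. The quoted sentence credits ITT with that job.

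This matters here because the protocol itself describes dropout that could differ between arms in timing and cause. Participants know their allocation, controls may leave when they hear it, and mentees may leave during the year for other reasons. If those who remain differ between arms, the Mentor Support versus control comparison can be biased. A report following this sentence could state that selective attrition had been accounted for when it had not.

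**Working it through.** **1. The plan's own figures.** The Sample size section gives power 0.85 at N = 120 and 0.80 at N = 108. For the between-subject factor of a repeated-measures ANOVA with k = 3 groups, m = 3 measurements, f = 0.25 and alpha = 0.05, and with a correlation rho = 0.5 between measurements (my assumption; none is given), the noncentrality is

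lambda = f² × N × m / (1 + (m − 1) × rho)

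- N = 120: 0.0625 × 120 × 3 / 2 = 11.25, df (2, 117), power 0.851.
- N = 108: 0.0625 × 108 × 3 / 2 = 10.125, df (2, 105), power 0.809.

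Both stated figures reproduce. The tolerated loss is 120 − 108 = 12 participants, which the section attributes to dropout or organisational causes. This allowance protects power and does nothing about bias.

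**2. What happens to a leaver under each permitted model.**

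| Participant | Repeated-measures ANOVA (standard) | Multilevel model with T1 as one of the repeated outcomes |
|---|---|---|
| Leaves, but measured at post-test and follow-up | Kept, in allocated arm | Kept, in allocated arm |
| Leaves after allocation, never reached again (T1 only) | Dropped listwise | T1 kept; valid only if dropout depends on observed data |
| Measured at post-test, missing at follow-up | Dropped listwise if all three times are analysed | Available times kept; same condition |

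ITT does real work in the first row. In the other two, the ANOVA route leaves only people with complete data, so it is in effect a completer analysis, even though the Abstract lists completers separately.

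**3. Size for the raw observed control mean.** Let p be the share of controls lost and delta the gap, in SD, between retained and lost controls. Then

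observed mean − true mean = mean(retained) − [(1 − p) × mean(retained) + p × mean(lost)] = p × delta

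The protocol gives no dropout rate by arm and no such gap, so every p and delta below is an assumption. With 40 controls, p = 10%, 20% and 30% means 4, 8 and 12 lost.

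| p | delta = 0.25 | delta = 0.5 | delta = 0.8 |
|---|---|---|---|
| 10% | 0.025 | 0.05 | 0.08 |
| 20% | 0.05 | 0.10 | 0.16 |
| 30% | 0.075 | 0.15 | 0.24 |

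Against d = 0.5, the middle case is 0.10 / 0.5 = 20%. The 30% row puts all 12 tolerated losses in the control arm (12 / 40). It is an extreme, and at a 0.5 SD gap it gives 0.15 / 0.5 = 30%.

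For the difference between arms (M = Mentor Support, C = control), the bias is p(M) × delta(M) − p(C) × delta(C). Mentee losses can therefore cancel the control term or add to it. The sign is not fixed by the documents.

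**4. What baseline adjustment does.** A large-sample simulation of one arm (true mean 0, T1–outcome correlation 0.5, log-odds of dropout falling by 1 per SD, all assumed) gave these biases in SD:

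| Control loss | Dropout depends on T1: raw | Adjusted for T1 | Dropout depends on the unseen outcome: raw | Adjusted for T1 |
|---|---|---|---|---|
| 10% | 0.045 | about 0 | 0.092 | 0.071 |
| 20% | 0.090 | about 0 | 0.172 | 0.132 |
| 30% | 0.128 | about 0 | 0.255 | 0.198 |

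An analysis that uses T1 removes the bias when T1 explains the dropout, and only part of it otherwise. So the model choice that the Data analyses section leaves open matters, and neither option covers every mechanism.

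**The case against.** The strongest reply is that this is a condensed article. Imputation models and sensitivity analyses usually belong in the full protocol or the SAP, and neither is shown. That is right, and the absence of such detail is not the point. The point is that the article does name a remedy, and the remedy does not do what is claimed for it.

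The second reply is that the section should be read whole: keep measuring people who leave, analyse them as allocated, and set the result beside a completer analysis. That is a coherent plan, and for leavers who are measured it works. The qualifier about feasibility may even apply to follow-up alone, leaving post-test measurement unqualified. Some people will still not be reached, and ITT has nothing to offer for them.

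Three stronger readings are tempting and should be resisted:

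- A reader might infer that the protocol expects controls to leave. It says only that they may, and it hopes that advance information will limit this.
- A reader might infer that the bias remains whichever model is used. A multilevel model, one of the two options, handles dropout explained by observed data.
- A reader might infer that dropout reasons are barred from the analysis of effect. The protocol states one use for them and excludes no other.

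It also stands that p × delta describes a raw mean, not the planned analysis of change over time.

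**Conclusion.** The point holds as a defect in a stated remedy. ITT alone does not account for selective attrition where outcomes are never obtained. If repeated-measures ANOVA is chosen, the analysis labelled ITT loses the very participants whose departure is the worry. If a multilevel model is chosen, the problem is partly handled, but the protocol neither commits to that model nor presents it as the remedy.

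The size is illustrative: 0.10 SD for the raw control mean at 20% control loss and a 0.5 SD gap, and 0.15 SD in the extreme case of 30%, against d = 0.5. These rest on assumed loss rates and gaps. They should not be read as the expected bias of the trial: baseline adjustment would reduce them where T1 explains the dropout, and losses among mentees could move the comparison either way. The correction should be made, but the documents do not show that the main result will be biased.

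**What to change.** Replace the sentence on intention-to-treat in the Selective attrition section with wording such as:

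> All randomised participants are analysed as allocated, using a likelihood-based multilevel model that includes everyone with a T1 measurement (or multiple imputation by arm with measured baseline predictors of dropout). Repeated-measures ANOVA on complete cases is not the ITT analysis. A sensitivity analysis shifts the missing outcomes separately by arm, informed by the documented dropout reasons, until the conclusion changes.

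The shift analysis is needed because the multilevel model and standard multiple imputation both assume that dropout is explained by observed data. Keep the plan to go on measuring people who leave, and report the timing of and reasons for dropout by arm.

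The cost is a modest amount of extra analysis and possibly wider intervals. No new data are needed, since the baseline measures and dropout reasons are already to be collected. The Trial status section reports recruitment and data collection still under way, so at that stage the change could precede analysis.
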